### Harms

3.16

The Data Nurse intervention is a non-pharmacological, educational and behavioral intervention embedded in routine district nursing care practice. Given its nature, no physical or medical harm to participants is anticipated. However, potential unintended effects will be monitored throughout the study. For older adults, the shared decision-making process may surface unmet care needs or emotional concerns related to declining independence, which could cause temporary distress. For district nursing team members, increased demands on time and workload associated with the intervention activities (completing the e-learning, facilitating shared decision-making conversations, and participating in team reflection sessions) may contribute to perceived burden. These potential harms will be explored through qualitative data collection (interviews and focus groups) and discussed during the monthly fidelity meetings with team leaders and data champions. No formal adverse event reporting procedures or data monitoring committee has been established, as this is a low-risk feasibility study of a behavioral intervention. Participants may withdraw from the study at any time without consequences for their care or professional role.

### Sample size

3.17

As this is a feasibility study, the sample size is not based on a formal power calculation. However, it is justified by pragmatic considerations and the available study population, in line with recommendations for feasibility studies of complex interventions (Eldridge et al., 2016). The study involves four organizations, each contributing 14 district nursing teams: 8 in the intervention group and 6 in the control group. Up to 168 district nursing team members are eligible, based on an average of 12 professionals per team. A participation rate of 50–65% is expected among district nurses (L'Ecuyer et al., 2023), resulting in approximately 84–109 participants. Each team supports an average caseload of 30 older adults (aged ≥65), yielding approximately 420 eligible participants across all teams. Based on expected recruitment rates in feasibility studies, a participation rate of approximately 50–70% is anticipated (Eldridge et al., 2016).

### Recruitment and participation

3.18

Recruitment will follow a multi-level approach. District nursing care organizations affiliated with the Data Nurse project will be invited to participate. Within these organizations, contact persons will distribute invitations to district nursing teams through internal communication channels such as newsletters, online bulletin boards and team meetings. Interested teams will be contacted by the research team, who will provide detailed information about the study and participation requirements. Individual team members within participating teams will decide voluntarily whether to participate in the research activities.

Older adults will be recruited by team members from participating teams, who will identify eligible older adults from their caseload and provide them with study information and an information letter. The recruitment procedure is visualized in Fig. 3.

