### Participants and eligibility criteria

3.8

District nursing teams members are eligible to participate if they are actively involved in patient intake, goal-setting, and care evaluation processes. Within teams allocated to the intervention group, all team members used the shared decision-making tools and dashboard as part of usual team practice. Individual team members could, however, decide whether or not to participate in the study's data collection (e.g., questionnaires and interviews). Older adults receiving care from team members who did not take part in data collection remained eligible for inclusion, as they still received the intervention through their team. Older adults are eligible if they are aged 65 years or older and currently receive district nursing care. Older adults must have sufficient cognitive capacity to provide informed consent and participate in interviews and in-person-centered shared decision-making. In addition, older adults must be able to complete the patient preparatory shared decision-making tool in Dutch, with help from their informal caregiver, if needed (Pel-Littel et al., 2020). Older adults are excluded if they have a life expectancy of less than three months. Also, older adults with a life expectancy of <3 months or with severe physical or cognitive impairments will be excluded from the study.

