### Allocation of participants

3.9

District nursing teams from participating organizations could voluntarily sign up for the study. Allocation to the intervention or control group was determined by the participating organizations, based on pragmatic factors such as team availability, staffing, and time resources. This pragmatic approach, which includes both an intervention and a control group, allows for assessing feasibility and exploring preliminary signals of effectiveness. It aligns with Eldridge et al., who highlight the importance of early impact indicators in feasibility studies of complex interventions (Eldridge et al., 2016). This design enables and informs the refinement of the intervention and future study planning.

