**Enrolment**										
	Eligibility screening	DNT members		**X**						
	Informed consent	DNT members + older adults		**X**						
	Baseline data collection	DNT members			**X**					
	Baseline data collection	Older adults			**X**					
	Allocation	DNT			**X**					

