## Study status

Study initiation commenced on June 2025. Recruitment and inclusion of district nursing teams took place in June 2025. Patient recruitment and inclusion will occur between June 15th and the end of September 2025. Qualitative analysis of interview and focus group data will be conducted from November to April 2026. Quantitative data analysis, including patient-reported outcome measures (PROMs) and care metrics, will be carried out between November 2025 and April 2026.

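### Team members who know their group decide which older adults to approach, so enrolment can differ by group; set one invite-all rule and report who was not enrolled

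*Protocol article*

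**What the plan says.** **Who recruits.** Section 3.18: "Older adults will be recruited by team members from participating teams, who will identify eligible older adults from their caseload". Team leaders then register participants in Castor.

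**How groups were formed.** Section 3.9: "Allocation to the intervention or control group was determined by the participating organizations, based on pragmatic factors such as team availability, staffing, and time resources". No concealment is described. Intervention teams take the e-learning and the dashboard workshop, so their members cannot be unaware of their group.

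**When.** The study-status statement says "Recruitment and inclusion of district nursing teams took place in June 2025" and "Patient recruitment and inclusion will occur between June 15th and the end of September 2025". Table 1 differs: its informed-consent row, for "DNT members + older adults", is marked in the May enrolment column, while allocation is marked in June.

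**On what criteria.** Section 3.8: "Older adults must have sufficient cognitive capacity to provide informed consent and participate in interviews and in-person-centered shared decision-making". Patients must also be able to complete the preparatory tool, and those with severe impairments are excluded.

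**How many.** Section 3.17 takes 30 older adults per team, about 420 in all, and says "a participation rate of approximately 50–70% is anticipated".

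**What the data are for.** Section 4.2 will report effect sizes and confidence intervals to help design a later trial. Older adults' FIM and TFA ratings of the preparatory tool are primary outcomes (section 3.14). Section 5.1 acknowledges selection bias, but only as a result of not randomizing.

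**The concern.** A patient's group is a property of the team, so whoever picks patients within a team knows which group each one will join. This is a second route to selection, separate from the choice of teams. It would remain if teams had been randomized, and it would remain if every baseline were taken on time.

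Two features allow the choice to differ by group. First, the criteria include fitness for shared decision-making and ability to complete the preparatory tool, yet control teams do not receive the tool (section 3.11) and must judge ability to use something they do not have. Second, the task ahead differs. Intervention patients complete the full tool, prepare for a goal conversation and fill in the TFA and CollaboRATE. Control patients complete 11 TOPICS-SF items and CollaboRATE (section 3.18.1.2).

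Two uses of the data are at stake. The between-group effect sizes could partly reflect who was invited. The intervention patients' FIM and TFA ratings could come from an unrepresentative part of the caseload, which matters in a study whose main question is feasibility.

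**Working it through.** **1. Does the recruiter know the group?** The study-status statement places team inclusion in June 2025 and patient inclusion from 15 June to the end of September. The abstract gives 4 June 2025 as the first recruitment. On these dates, patients enter as or after teams are placed, and most of the window falls within the intervention period. Table 1 alone suggests consent in May, before allocation. The two must be reconciled. The dated statements favour the reading that the group was known.

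**2. Would the planned reporting show the problem?** Section 4.2 calculates retention and participation as percentages of those initially enrolled, not of those eligible or approached. Baseline characteristics are collected on participants only. A baseline comparison of the two groups would mix differences between teams with selection within teams. Only a comparison of enrolled with not-enrolled clients, within each group, separates the two.

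**3. The plan's own figures.**
- 14 × 30 = 420; 420 × 0.50 = 210 and 420 × 0.70 = 294. This reproduces the abstract's 210–294.
- Intervention: 8 × 30 = 240, of whom 120–168 enrol.
- Control: 6 × 30 = 180, of whom 90–126 enrol.
- Not enrolled: 420 − 294 = 126 to 420 − 210 = 210, that is 30–50% of the pool. This figure includes patients who decline.

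**4. An upper-end illustration.** None of the following assumptions is in the document. Suppose all non-participation is staff selection, on a normally distributed inclination to invite that correlates r with the outcome in the intervention group and 0 in the control group. With participation p, the spurious difference in SD units is

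r × φ(z)/p, with z = Φ⁻¹(1 − p).

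The factor φ(z)/p is 0.798 at p = 0.5 and 0.497 at p = 0.7.

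| r | p = 0.5 | p = 0.7 |
|---|---|---|
| 0.1 | 0.08 | 0.05 |
| 0.2 | 0.16 | 0.10 |
| 0.3 | 0.24 | 0.15 |

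If the control group has its own correlation and the same p, r becomes the difference between the two correlations. Equal correlations give zero. If staff approach every eligible client, staff selection is also zero, whatever p is.

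**5. Set against precision.** The 95% half-width for a difference of two means, in SD units and ignoring clustering, is 1.96 × √(1/120 + 1/90) = 0.27 at 50% and 1.96 × √(1/168 + 1/126) = 0.23 at 70%. With an assumed ICC of 0.05, the design effect is 1 + 14 × 0.05 = 1.7 for 15 patients per team and 1 + 20 × 0.05 = 2.0 for 21. The half-widths become 0.36 and 0.33. At the top of the illustrated range the bias approaches the unclustered half-width at 50% participation, and the interval would not reveal it.

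**The case against.** There is a serious case on the other side, and much of it limits the point.

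- **Fig. 3 is not shown.** The recruitment flowchart, or the full protocol behind the article, may contain an invitation rule. All that can be said is that the visible text gives none.
- **Participation is not selection.** The 50–70% includes patients who decline, since entry is the older adult's own decision. The figures in step 4 are therefore upper-end for any given r.
- **Control staff may select too.** CollaboRATE is collected in both groups, so control patients also rate their care encounters, and the written criteria are the same. Setting r = 0 in control is an assumption; similar selection in both groups would largely cancel.
- **Change from baseline helps.** Section 4.2 explores change, which removes part of any stable difference in level. It does not remove a difference in the chance of improving. It also does not help the older adults' TFA, which Table 1 schedules only at close-out.
- **Effectiveness is exploratory.** Section 3.13 rules out formal hypothesis testing, and the primary outcomes are descriptive and confined to the intervention group. This lowers the consequence but does not remove it: the effect sizes are meant to inform the next trial, and section 5.1 says the findings will inform whether a larger trial is warranted.

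A reader might go further and infer that intervention nurses will pick abler or more cooperative patients, that the nurse who recruits is the one who holds the conversation, or that the comparison is biased by a known amount. The document supports none of these. It says that team members recruit and that district nurses hold the conversations, without saying they are the same person, and it gives nothing from which a direction or size could be derived.

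**Conclusion.** The point stands as a risk created by a stated procedure, not as a demonstrated bias. Staff who know their group identify patients using criteria that need judgement. The visible text gives no common invitation rule, and section 5.1 does not mention this route. It can bias the exploratory between-group effect sizes and can make the intervention patients' FIM and TFA ratings unrepresentative.

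The range of 0.05 to 0.24 SD shows only what could happen for r between 0.1 and 0.3, with all non-participation due to staff selection in the intervention group alone and nothing removed by change from baseline. The conclusion also rests on the study-status dates. If consent truly preceded allocation, as Table 1 marks it, the point weakens. The change is worth making because it is cheap and the estimates feed later decisions.

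**What to change.** **Section 3.18, both groups.**
- Draw from the electronic nursing record a list of all clients aged 65 or older in care at the start of recruitment, and add new clients until the end of September. A list fixed on one date would miss clients who enter care during the window.
- Invite every listed client with the same letter unless a listed exclusion criterion applies. Record the criterion in Castor before the client is approached.
- Report by group the numbers listed, excluded by reason, approached, declined and enrolled.

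Teams would still judge the softer exclusions knowing their group, but those judgements would be visible and countable.

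**If recruitment is complete.** Have each organization produce the list retrospectively, subject to any approval needed. Report an aggregate comparison of enrolled with not-enrolled clients by group, on age, sex, care hours and last care need scores.

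**Section 5.1 and reporting.** Name this bias separately from the choice of teams. Present the between-group effect sizes beside the comparison, with a caution that matches what it shows. A rule to withhold them would need a threshold, and some difference will always appear with six to eight teams per group.

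**Table 1 and study status.** Reconcile the order of older adults' consent and team allocation.

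**Cost.** One record query per team, which the organizations' business intelligence staff should be able to run since they already connect these records to the dashboard; some team-leader time; and possibly a lower uptake percentage.

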**Fig. 3 fig0003:**
[figure not shown]
Recruitment flowchart.

Upon agreement to participate, team members and older adults will receive an information letter and provide written informed consent. Team leads register participating older adults in Castor for data collection. Participants can withdraw from the study at any time without consequences for their care.

#### Data collection

3.18.1

Data will be collected over a five-month period from June to November 2025, using a combination of questionnaires, interviews, focus groups, and electronic nursing record data. Table 1. presents the complete schedule of enrolment, interventions, and measurements. Team members will complete questionnaires online through Castor. Older adults will complete paper-based questionnaires, which will be entered into Castor by researchers. Primary outcomes (feasibility, acceptability, fidelity, barriers and facilitators, and experiences) will be assessed exclusively in the intervention group, as these relate directly to the use of the intervention. Secondary outcomes (self-reported independent functioning, patient-reported shared decision-making, and nursing care delivery patterns) will be assessed in both groups to allow comparison.

**Table 1 tbl0001:** Schedule of enrolment, interventions, and assessments (SPIRIT).

		Population	Instrument	Trial period						
				Enrolment	Allocation	Post-allocation				Close-out
Timepoint				-t₁	0	*t*₁	*t*₂	*t*₃	*t*₄	*t*₅
				*May*	*Jun*	*Jul*	*Aug*	*Sep*	*Oct*	*Nov*
**Enrolment**										
	Eligibility screening	DNT members		**X**						
	Informed consent	DNT members + older adults		**X**						
	Baseline data collection	DNT members			**X**					
	Baseline data collection	Older adults			**X**					
	Allocation	DNT			**X**					
**Intervention preparation**										
	Use patient preparatory tool shared decision-making	Older adults (I)			**X**					
	shared decision-making e-learning	DNT members (I)			**X**					
	Follow dashboard workshop	Data champions + older adults (I)			**X**					
**Intervention or comparator**										
	Data Nurse intervention cycle*	DNT member (I)			**X**	→	→	→	→	
	Care as usual	DNT members (C)			**X**	→	→	→	→	
**Assessments: Primary outcomes**										
***Feasibility***										
	Feasibility of intervention	DNT members (I)	*FIM*		**X**					**X**
	Feasibility of patient preparatory tool shared decision-making	Older adults (I)	*FIM*		**X**					**X**
***Acceptability***										
	Acceptability of intervention	DNT members (I)	*TFA*		**X**					**X**
	Acceptability of patient preparatory tool shared decision-making	Older adults intervention team	*TFA*							**X**
***Fidelity***										
	Adherence to intervention components	DNT members (I)	*Self-developed questionnaire*			**X**	**X**	**X**	**X**	**X**
	Delivery monitoring (Kotter framework)	Data Champions (I)	*Monthly meetings*			**X**	**X**	**X**	**X**	**X**
***Barriers and facilitators***										
	Implementation factors	DNT members (I)	*TDF*		**X**					**X**
	shared decision-making -specific experiences and barriers	DNT members (I)	*Self-developed*							**X**
***Experiences***										
	Experiences with shared decision-making	DNT members (I)	*Self-developed questionnaire*							**X**
	Experiences with shared decision-making	Older adults (I)	*Interviews*							**X**
	Intervention experiences	DNT members (I)	*Focus groups*							**X**
**Assessments: Secondary outcomes**										
Self-reported independent functioning	Health and functioning across domains	Older adults (I+C)	*Modified TOPICS-SF*		**X**					**X**
Patient-reported shared decision-making	Level of shared decision-making from patient perspective	Older adults (I+C)	*CollaboRATE*		**X**					**X**
Nursing care delivery patterns	Visit frequency, delivery mode, care hours	DNT members (I+C)	*ENR data*		**X**					**X**
**Additional data collection**										
**Care as usual**	Experiences with usual care	DNT members (C)	*Interviews*							**X**

I=Intervention Group; C=Control Group. DNT: District Nursing Team. SDM: Shared Decision-making.

##### Older adults

3.18.1.2

At baseline, characteristics of older adults who participate will be collected. These include year of birth, gender, marital status, living situation, highest level of education completed, country of birth, reason for receiving care, frequency of contact with district nursing, financial concerns, and care or support from the municipality. Additional qualitative information will be collected on older adults' living situation and municipal support.

Older adults in the intervention group will complete the patient-shared decision-making preparatory tool, based on the TOPICS-SF and covering self-reported independent functioning, general health, pain, emotional well-being, social activities, quality of life, and personal goals and wishes. In addition, they will complete the TFA questionnaire on acceptability of the patient preparatory tool shared decision-making and the CollaboRATE questionnaire on patient-reported involvement in shared decision-making. Individual interviews will be conducted to explore their experiences with person-centered shared decision-making.

Older adults in the control group will complete selected domains of the TOPICS-SF, specifically the self-reliance domain (10 items) and the social activities domain (1 item, to measure self-reported independent functioning, as well as the CollaboRATE questionnaire.

## Data analysis

4

Quantitative and qualitative data will be analyzed separately and subsequently integrated to provide a comprehensive understanding of the intervention's feasibility, acceptability, fidelity, experiences, barriers, and facilitators, and preliminary effectiveness.

### Qualitative analysis

4.1

Interview and focus group data will be analyzed using thematic analysis following the six-phase framework of Braun and Clark (Braun and Clarke, 2014). Audio recordings will be transcribed verbatim using Microsoft Teams and imported into MAXQDA (MAXQDA, 2024) for systematic coding and theme development. An inductive coding approach will be used to identify patterns related to the outcomes to Data Nurse intervention. To enhance analytic rigor, two researchers will independently code the transcripts, with discrepancies resolved through discussion. Data triangulation between patient interviews and nursing professionals' focus groups will strengthen the comprehensiveness.

### Quantitative analysis

4.2

Paper questionnaires will be manually entered into Castor to ensure a complete central database. Data will be checked for outliers, inconsistencies, and missing values prior to analysis. Likert scale responses will be treated as ordinal variables. All statistical analyses were conducted using R, version 4.4.3, an open-source software environment for statistical computing and graphics (Posit team, 2025). Demographic characteristics of participants will be summarized using descriptive statistics (means, standard deviations, frequencies, and percentages). Primary outcomes, including feasibility (FIM), acceptability (TFA), fidelity, and barriers and facilitators (TDF), will be analyzed descriptively. Retention and participation rates will be calculated as percentages of initial enrolment to assess engagement throughout the study. For secondary outcomes (self-reported independent functioning, patient-reported shared decision-making, and nursing care delivery patterns), changes between baseline and follow-up will be explored descriptively. Effect sizes and confidence intervals will be reported to inform the design of a future effectiveness trial.

### Integration

4.3

Quantitative and qualitative findings will be integrated using a narrative synthesis approach. (Fetters et al., 2013)Data triangulation between older adult interviews, team member focus groups, and quantitative outcomes will be conducted to provide a comprehensive understanding of the intervention's feasibility and preliminary effectiveness (Creswell, 2022).

